#### Education control

The content of this class is based on information from the American Thoracic Society, American College Chest Physicians, and the *Global Obstructive Lung Disease Patient Guide*[69–74]. Educational modules include: anatomy of the lungs, COPD, managing COPD symptoms, smoking cessation, diagnostic tests, understanding COPD meds, managing acute exacerbations, managing stress, exercise, nutrition, sleep, mental health, oxygen therapy, surgical options, pulmonary rehabilitation, and advance care planning. Time is spent with both didactic as well as informal group discussion moderated by the instructor. The instructors have explicit instructions to moderate discussions and not make any recommendations regarding an individual’s treatment.

#### MBB intervention

The MBB intervention is comprised of the breathing techniques of the tai chi exercise program; however, all techniques are performed in a seated position. This intervention removes some elements of physical activity (no aerobic activity, no lower extremity strengthening and stretching, less core strengthening), while retaining breathing and mindful awareness.

The overall goals of the breathing intervention are to increase the efficiency of gas exchange, enhance awareness/mindfulness of the mechanics of breathing, and promote relaxation of both physical body and mind. Four traditional inter-related techniques are taught; detailed descriptions of these can be found in traditional and modern tai chi and *qigong* publications [75–78]. 1) *renewing the body with breath* is a simple relaxation technique that employs the breath and imagery as a focusing tool to release physical and emotional tensions; 2) *mindful breathing* cultivates inner awareness of the breath as air and its consequent internal pneumatic and hydraulic pressures travel from the nostrils to the lower abdomen, and back out; 3) *ocean breathing* emphasizes diaphragmatic breathing and expansion and contraction of the lower abdomen; and 4) *balloon breathing* emphasizes effortless inhalations and a prolonged exhalation cycle relative to inhalation.

Each of the techniques was chosen to emphasize different aspects of MBB relevant to COPD rehabilitation. The expectation is that over time these methods will become integrated into usual breathing patterns during daily activities. Subjects in class are explicitly taught to incorporate the techniques into simple activities of daily living (for example, while reading or talking on the phone). The protocol also begins with the same series of seated warm-up exercises that are employed in the tai chi intervention that particularly target awareness and flexibility of the upper torso and rib cage. Subjects who complete all study requirements have the option of joining a class of their choice (one of the two groups to which they were not randomized). These subjects do not undergo additional testing but are monitored for AEs.

### Primary measures

All research staff performing outcome testing are blinded to participants’ intervention allocations. Table 1 details the schedule of evaluations.

**Table 1 Tab1:** **Schedule of evaluations**

Outcome	Measurement/instrument	Month		
		0	12	24
Physical functioning				
Exercise capacity	**6-minute walk test (6 MW)***	X	X	X
	Bicycle cardiopulmonary exercise test**			
Strength/flexibility	Chair sit and reach	X	X	X
	Chair stand			
Physical function	PROMIS physical function	X	X	X
Health-related quality-of-life and symptoms (HRQL)				
COPD-specific HRQL	**Chronic respiratory disease questionnaire (CRQ)***	X	X	X
Dyspnea	UCSD shortness of breath questionnaire;	X	X	X
	MMRC dyspnea scale			
Fatigue	PROMIS fatigue	X	X	X
Psychosocial functioning and support				
Self-efficacy	COPD self-efficacy scale	X	X	X
Mood	Center for epidemiologic studies-depression scale (CES-D)	X	X	X
Stress	Perceived stress scale	X	X	X
Perceived social support	Multidimensional scale of perceived social support	X	X	X
Pulmonary function				
Spirometry and lung volumes	Standard pulmonary function tests	X	X	X

*Primary measures. **Cardiopulmonary exercise test (n = 50) will be done in a subset of patients. PROMIS, Patient-Reported Outcome Measurement Information System; COPD, chronic obstructive pulmonary disease; UCSD, University of California, San Diego; MMRC, Modified Medical Research Council.

#### Six-minute walk test

This is a standardized assessment that measures the maximum distance walked in 6 minutes [79]. Subjects are read standardized, scripted instructions and informed when there are 3 minutes and 1 minute before the end of the test. Subjects are allowed to stop as often as they need and to use supplemental oxygen if usually prescribed for activity. The 6-minute walk test has been shown to be an independent correlate of COPD prognosis and survival [80, 81].

#### Disease-specific HRQL measure

The main HRQL measure is the disease-specific chronic respiratory disease questionnaire (CRQ). This validated instrument is one of the most commonly employed health status measures for COPD. It consists of 20 items covering four domains - dyspnea, fatigue, emotional function and mastery. Items are scaled on a 7-point modified Likert scale, with higher scores indicating better HRQL [82]. We use the self-administered, standardized version. Our main outcome is a total CRQ score calculated by the sum of individual responses divided by the number answered (mean response).

### Secondary measures

#### Cardiopulmonary exercise test

In a random subset (n = 50 total), participants perform a symptom-limited exercise test using a bicycle ramp protocol to determine peak oxygen uptake (VO_2_) and exercise endurance. Testing is done on an electronically calibrated upright bicycle, with expired gas analysis under continuous electrocardiographic monitoring. Breathlessness and leg fatigue are measured using the Borg scale of 1 to 10 during the test. Breath-by-breath respiratory gas analysis is performed using a SensorMedics (Yorba Linda, CA, USA) metabolic cart. Peak values are averaged from the final 20 seconds of the test. Peak VO_2_ has been shown to correlate with cardiac output and skeletal muscle blood flow and predict mortality in COPD [83].

#### Strength and flexibility

The chair stand test assesses lower body strength and endurance. Subjects are instructed to rise to a full standing position and then return to a seated position with arms folded across their bodies as many times as possible within 30 seconds. This validated test has been used in numerous populations with age and gender specific normative data available [84]. The chair sit and reach assesses lower body flexibility, primarily the hamstring, and is a modification of the original sit and reach, developed for use in older or deconditioned populations to decrease risk of injury in those with back pain or limited range of motion [85].

#### Dyspnea

The University of California, San Diego (UCSD) shortness of breath questionnaire is a 24-item self-administered instrument that assesses the degree to which patients feel short of breath while performing 21 different activities of daily living. Respondents rate symptoms on a 6-point scale from not at all to maximally or unable to do because of breathlessness [86]. The Modified Medical Research Council (MMRC) dyspnea scale is a 4-point scale assessing dyspnea severity, with a score of 4 indicating that the patient is too breathless to leave the house or becomes breathless when dressing or undressing. This scale predicts the likelihood of survival among patients with COPD and correlates well with other scales and health status scores [87]. This scale is one of the four components of the body mass: airflow obstruction: dyspnea: exercise capacity (BODE) index, a validated multidimensional grading system for COPD that has been shown to be a better predictor of mortality than FEV_1_ alone [88].

#### Self-efficacy

The COPD self-efficacy scale (CSES) was developed to identify situations during which patients with COPD lack confidence in their ability to manage or to avoid breathing difficulties. The situations include times of negative affect (*when I feel down or depressed*), intense emotions, physical exertion, at-risk behaviors (*when I overeat*), or adverse weather/environmental conditions. Patients rate the level of confidence they feel, ranging from not confident at all to very confident, in managing or avoiding breathing difficulties during 24 different situations. The CSES has high internal consistency (*r* = 0.95) and test-retest reliability (*r* = 0.77) [89].

#### Emotional status/mood

The Center of Epidemiology Studies-depression scale (CES-D) is a general measure of psychological impairment, primarily depressive symptoms, that has been used extensively in epidemiology studies [90]. It is a validated instrument consisting of 20 items, including feelings of depression, worthlessness, loneliness, energy level and fear. Participants are asked to report how often they experienced the symptom during the past week using a 4-point ordinal scale (rarely or none of the time; some or little of the time (1 to 2 days); occasionally or moderate amount of the time (3 to 4 days); most or all of the time (5 to 7 days). A score <15 indicates no depression. The CES-D has high internal consistency (*r* = 0.90) and a test-retest reliability of 0.51 [91, 92].

#### Physical function and fatigue

We use the PROMIS Physical Function-Short Form 10a questionnaire to track patients’ physical functioning, and the PROMIS Fatigue Short Form 7a to track patients’ fatigue. The Patient-Reported Outcome Measurement Information System (PROMIS®) instruments funded by the National Institutes of Health are based on modern measurement theory and include the application of mixed methods approaches for instrument development. Both forms are short validated instrument with seven to ten items, each with five response options on an ordinal scale (not at all, a little bit, somewhat, quite a bit, very much) [93, 94].

#### Perceived stress and social support

The perceived stress scale is a measure of the degree to which situations in one's life are appraised as stressful. We will use the 10-item version of this instrument which we have used in our prior tai chi trials and which has been shown to have good reliability and validity [95]. The multidimensional scale of perceived social support is a validated instrument that will be used to assess the degree of perceived social support provided in each group. It consists of 12 items covering subscale areas of family, friends, and significant others [96].

#### Pulmonary function tests

Spirometry and lung volume measurements will be performed using rolling-seal volume displacement spirometers (Collins CPL Raptor, Louisville, CO, USA), following American Thoracic Society standards for quality and reproducibility [97]. Lung volumes are performed via plethysmography. Lung volumes, such as total lung capacity (TLC) and functional residual capacity, add information about hyperinflation from COPD that may negatively affect respiratory muscle function. The inspiratory-to-total lung capacity ratio (IC/TLC) may be a particularly useful index of resting airflow limitation and lung hyperinflation that correlates with exercise capacity [98].

### Other data collection

#### Physical activity

To track participants’ level of physical activity outside of exercise classes, we use the Community Health Activities Model Program for Seniors (CHAMPS) physical activity questionnaire for older adults [99]. CHAMPS is a 41-item validated instrument in the elderly, which covers physical activity from several domains, including leisure, household, and occupational. Weekly frequency and total time spent allows estimation of caloric expenditure. In addition, we use the Moy physical activity checklist specifically to measure activity in patients with COPD [100]. A higher number of daily checklist activities performed is associated with better indices of COPD health, including higher FEV_1_ and lower BODE index.

#### Qualitative interview

We also perform semi-structured qualitative exit interviews with participants in all groups to further explore areas not captured in our standardized quantitative instruments. Questions probe participants’ experiences with the program overall; changes in physical, mental, or social function specific to the intervention; changes in illness perception; experiences with practicing the intervention; and expectations and beliefs about mind-body therapies. These open-ended questions may yield additional insights into understanding the mechanism of a mind-body exercise program. Each interview session is audio recorded, then transcribed verbatim.

#### Adherence

Adherence is defined as greater or equal to 70% of intervention classes attended. During phase 1 in the first 12 weeks, compliance with home practice in the tai chi and MBB arms is tracked through home practice logs that are completed at each class. During phase 2 in the second 12 weeks, those not randomized to continued classes are queried about home practice once a month by phone.

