### Interventions

Tai chi, MBB, and education classes are conducted twice weekly for one hour each for the first 12 weeks. In the second 12 weeks of the study, participants in the tai chi class may be assigned to continue tai chi classes once weekly for an additional 12 weeks. Instructors who administer the tai chi and MBB interventions are senior tai chi students and certified graduates of a 2.5-year instructor training program that includes training in meditative breathing. The average training experience of the four study instructors is 19 years.

Importantly, the tai chi instructors also administer the education class to minimize the variability with respect to instructor type, personality, and training. Chairs are provided for seated warm-up, breathing exercises and resting, as well as for stability as needed when performing standing tai chi exercises. Subjects in tai chi and MBB groups receive a 45-minute video as well as a separate audio file of the exercises taught in class, and are given detailed instruction about specific exercises, and encouraged to practice outside of class three times a week (for at least 30 minutes).

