#### Safety and adverse event monitoring

Interview data are used to document patients’ use of health care during the study period. Medical record review is conducted for details of hospitalizations for AE reporting. At each testing visit at baseline, 12 and 24 weeks, we ask specifically about medical symptoms in the past 12 weeks such as muscle strain, fainting/loss of consciousness, dizziness, worsening shortness of breath or COPD exacerbation, worsening fatigue, falls, palpitations, psychological stress, or other AEs. For any symptom ascertained, we further document the patient’s perception of relatedness to the intervention or testing, severity, any required change in medications, and any further medical care, hospitalization or ER visit. For hospitalizations and ER visits, we further ascertain discharge diagnosis and results of major cardiopulmonary tests or procedures performed. During the intervention, occurrences of adverse events are also queried by instructors and captured in the attendance log, which subjects complete during each class. If a potential AE is reported, study staff contact the participant for further details to determine if a reportable AE has occurred and if so, document the type, whether expected or not, relatedness to the study, and severity. Serious AEs are defined according to our institutional review board’s policy to be an event that is life-threatening, requires hospitalization, results in persistent or significant disability/incapacity or death. Incidents are reported to the IRB, our sponsor, and our Data Safety and Monitoring Board (DSMB) as appropriate.

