##### Exploratory aim 1 (dosage)

With respect to examining dosage of tai chi, we will compare the change in all outcomes between the two tai chi groups (12-week versus extended 24-week intervention) using ANCOVA and the Wilcoxon rank sum test as appropriate, similar to our primary aims. We will further assess adherence to the continued classes from 12 to 24 weeks. We will also analyze home practice hours (in both groups), and total practice hours (class plus home practice in the 24-week class group) and compare groups using the Wilcoxon rank sum test. Clinical data obtained through patient interview will be analyzed using descriptive statistics.

Particularly in the intervention groups, we will describe patient attendance at classes and compliance with home practice, and examine whether compliance or dosage is associated with clinical outcome.

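### Phase 2 home practice is collected by a monthly phone call only from tai chi patients who stop classes, yet practice hours are compared with those who continue, so part of any difference may reflect the capture method

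*Protocol article*

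**What the plan says.** All references are to the protocol article.

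- **Adherence, phase 1.** Up to week 12 the rule is: "compliance with home practice in the tai chi and MBB arms is tracked through home practice logs that are completed at each class".
- **Adherence, phase 2.** From week 12 to week 24 the rule is: "those not randomized to continued classes are queried about home practice once a month by phone". Nothing is said about how home practice is recorded for patients who continue.
- **Interventions.** In phase 2, "participants in the tai chi class may be assigned to continue tai chi classes once weekly for an additional 12 weeks". Continuing patients are therefore seen every week. The article also encourages home practice three times a week for at least 30 minutes.
- **Exploratory aim 1 (dosage).** The plan is to analyse "home practice hours (in both groups), and total practice hours (class plus home practice in the 24-week class group) and compare groups" with the Wilcoxon rank sum test. It will also examine whether compliance or dosage goes with clinical outcome.
- **Safety and adverse event monitoring.** All participants get a structured question: "At each testing visit at baseline, 12 and 24 weeks, we ask specifically about medical symptoms in the past 12 weeks". There is a further route while classes run: "occurrences of adverse events are also queried by instructors and captured in the attendance log, which subjects complete during each class".

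No section aligns the two ways of collecting home practice or mentions the difference as a limitation.

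**The concern.** The second randomisation makes the two tai chi groups comparable as patients. It does not make their practice hours comparable if the hours are collected in different ways. A difference in instrument that follows the randomised group does not average out with more patients, and no analysis can separate it from a true difference in practice.

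At stake is the reading of the practice data in Exploratory aim 1. A difference in reported hours could be taken as an effect of continued classes on home practice when some of it is an effect of how often, and in what setting, patients were asked. The same data feed the analysis relating dosage to outcome, where reported dose would carry a group-specific error.

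A smaller matter of the same kind concerns adverse events. In phase 2 the in-class prompt reaches only patients who still have classes, whereas the 24-week question reaches everyone.

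**Working it through.** The article states no figure on this point that could be reproduced. The check sets the sections side by side, counts contacts, and then illustrates sensitivity under assumed inputs.

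**1. Capture by group in phase 2**

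| | Stopped tai chi | Continuing tai chi |
|---|---|---|
| Home practice, method stated | Monthly phone query | None stated |
| Home practice, method implied | – | Log at each class, as in phase 1 |
| Contacts in 12 weeks | 12 / (52/12) = 12 / 4.33 = 2.8, about 3 | 12 × 1 = up to 12 |
| Adverse events, common route | 24-week structured question | 24-week structured question |
| Adverse events, extra route | – | Query and log at each class |

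There are two readings. If class logs continue, the comparison sets up to 12 log entries against about 3 phone reports. If they do not, the planned comparison has no stated source of phase 2 home practice for one group. The plan needs a correction on either reading.

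**2. What a reporting difference would do to hours (illustration)**

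Input from Interventions: 3 sessions × 0.5 h = 1.5 h per week. This is the encouraged minimum, not observed practice. Over 12 weeks: 1.5 × 12 = 18 h. If one method captured 20% fewer hours (assumed), the spurious difference would be 0.20 × 18 = 3.6 h with identical true practice.

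**3. What it would do to the Wilcoxon test (illustration)**

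Simulation settings: 21 per group (the article's figure for this comparison), two-sided 0.05, log-normal hours, equal true practice, one group's reported hours multiplied by a constant. The coefficients of variation (CV) of 0.5 and 0.8 are assumptions, as are the multipliers.

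| Reported / true hours in one group | P(p<0.05), CV 0.5 | P(p<0.05), CV 0.8 |
|---|---|---|
| 1.0 | 0.045 | 0.051 |
| 0.9 | 0.114 | 0.076 |
| 0.8 | 0.312 | 0.165 |
| 0.7 | 0.651 | 0.341 |

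A 10% reporting difference does little. At 20% the false-positive rate is roughly 17 to 31%, and at 30% roughly 34 to 65%. These figures apply to phase 2 home practice taken alone. If the analysis also counts weeks 0 to 12, that portion is captured in the same way in both groups and the effect is diluted.

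**4. What is not touched**

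The primary comparison is tai chi against education at 12 weeks, before the methods diverge. The comparisons of CRQ and 6-minute walk between 12 and 24 weeks of tai chi use test visits common to both groups and do not depend on practice hours.

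**The case against.** The strongest reply is that half of the contrast is inferred. The article ties the class logs to phase 1 and is silent on continuing patients in phase 2. A data-collection form is the kind of detail that a condensed article leaves to the full protocol. This stands as a limit on the wording: a definite difference in method cannot be asserted. It does not dispose of the point, because the article itself specifies the phone call for one group only and then plans a comparison between the groups.

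A reader might go further in three ways that the documents do not support.

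- **One-week recall against four-week recall.** The article gives how often patients are contacted, not the period they are asked to recall, nor whether the log is a diary. The size and direction of any bias are unknown.
- **Phase 2 adverse event frequencies will look higher in continuing patients.** Every group gets the same structured 24-week question. Interviews on health-care use and record review for hospitalisations are not confined to class attenders. The Safety/feasibility section plans only descriptive frequencies per arm, no separate comparison of the two phase 2 tai chi groups, and a safety criterion resting on treatment-related serious events. Extra prompts may raise counts in continuing patients; no more can be said.
- **The dosage result itself is biased.** The CRQ and walk-test comparisons do not use practice hours, and the article does not say that practice hours are meant to interpret them.

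It is also fair to say that a monthly item is coarser than a weekly log. Any class-log data should therefore be kept, though not used for the between-group comparison.

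**Conclusion.** The point holds in a limited form. In phase 2 a home-practice method is stated for one re-randomised tai chi group and not for the other, and the two are then compared on practice hours. Part of any difference in phase 2 hours may therefore reflect the capture method.

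This rests on two readings: that continuing patients are not also phoned monthly, since the article assigns the call only to the others; and that the practice-hours comparison includes weeks 12 to 24. The 3.6 h and the inflated rejection rates in the working show what an assumed reporting difference would do; they do not estimate what will happen.

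The reach is confined to the practice-hours comparison and the dosage-outcome analysis. The correction is worth making because it is cheap and because the difference cannot be repaired in analysis once the data are in. The adverse event aspect is a minor matter of tabulation.

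**What to change.** 1. In the Adherence section, state that in phase 2 both re-randomised tai chi groups are asked the same home-practice question, with the same wording and recall period, once a month on the same schedule. Continuing patients can be asked by phone or in class; the phone keeps the mode identical as well.
2. In Exploratory aim 1, state that the between-group comparison of phase 2 home practice, and the home-practice part of phase 2 total hours, uses this common item. Say which weeks the comparison covers. Keep any class-log data as supplementary description.
3. If phase 2 adverse event frequencies are tabulated by arm, show those from the 24-week interview common to all arms separately from events found only through class logs.

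The cost is about three short questions per continuing patient, which at 21 per group is 21 × 3 = 63 questions in all, put to people already seen weekly, plus one split in the adverse event table. The price in information is a coarser measure than a weekly log for the comparison. The Trial status section describes recruitment as active, so the change could apply to patients yet to enter phase 2. Those already past it would lack the common item, and the report should say so.
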